## 1. Introduction

Nearly 1.1 M Europeans suffer a stroke each year (17 M worldwide), which adds to 33 M stroke survivors [1]. Mortality is about 15% by 1 month, 25% by 1 year, and 50% by 5 years. A third of survivors experience disability (modified Rankin Scale scores 3–5) five years after having a stroke, due to physical, cognitive, and/or emotional deficits [2,3]. Much of the scientific efforts focus on medical programs involving acute care and inpatient rehabilitation. However, long-term disability often occurs and patients may continue to experience serious daily difficulties.

Outpatient neurorehabilitation programs are quite dissimilar, ranging from specialized interdisciplinary programs (involving different configurations of therapies) to limited individual therapies [4]. The need for better post-stroke care is still an issue. Indeed, the late rehabilitative phase is essential to both patients and their caregivers. Patients must receive a current continuum program instead of patchy modules of care shaped by a specific purpose with separate accountability [5]. Additionally, they need to understand the objectives of each phase of post-acute rehabilitation in different contexts and comprehend the challenges encountered at each level for the development of their empowerment and the appropriation of their future.

The notion of reaching a plateau in stroke recovery is questioned by a growing number of studies [6]. Accordingly, there is a need to design and assess therapeutic interventions in neurorehabilitation that promote sustained recovery from stroke over time [7,8]. Multidisciplinary programs need to be developed to cover the complex stroke continuum with the ultimate goal of reducing its large burden [7]. There is growing evidence that a multidisciplinary and cross-sectoral approach is pivotal to allow optimal post-stroke functional recovery [9,10].

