#### 2.1.2. Primary Efficacy Endpoint

The Functional Independence Measure (FIM; lasting 30–45 min) (time frame: Changes from baseline to week 22; changes from week 22 to week 48) is an 18-item 7-point Likert scale evaluating physical, psychological, and social function, indicating the amount of assistance required for each task. A final total score is obtained ranging from 18 (complete dependence/total assistance) to 126 (complete independence) [37].

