#### 2.1.4. Sample Size and Recruitment

From the related data [47], the sample-size calculation was based on a minimum reasonably significant difference in the primary outcome (Functional Independence Measure) of 22 points with a standard deviation of σ = 28.43 [48]. To detect that difference with a power of 80% using a two-sample *t*-test at a two-sided significance level of 5%, a total of 44 patients in the randomized arms (22 per arm) will be required. We will recruit 52 patients into the study, to allow for an attrition rate of around 20%.

Recruitment will be conducted during a 12-month period. The study will end when the last patient enrolled undergoes a neurological evaluation to determine the durability of functional recovery.

The end-of-treatment assessment will be completed within two weeks of the end of 22 weeks of treatment and the end-of-protocol assessment will be completed 26 weeks after the end of treatment. The protocol began in the fourth quarter of 2021 and will run through the third quarter of 2024.

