### 2.2. Selection/Treatment of Subjects

#### 2.2.1. Participants

Participation in the study will be proposed to every patient hospitalized at the CHSF after a stroke, fulfilling the inclusion criteria. Patients will be drawn at random to build the two arms of the study. The study participants will be adult males or females with a moderate to severe disability (Rankin score ≥ 3 and ≤4 at baseline). Each participant will present written informed consent in accordance with the Declaration of Helsinki. The data will be anonymized and properly stored to respect the confidentiality of sensitive medical data and EU GDPR legislation. Those responsible for the selection and inclusion of patients are the neurologists of the Neurology Service and Neurovascular Unit of the CHSF coordinated by [name], head of department and principal investigator. A certificate of non-contraindication to hippotherapy will be established by the neurologists of the CHSF for each single patient. In case of a patient’s withdrawal, he/she will continue to benefit the planned care with no impact on its quality.

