#### 2.4.1. Analysis Population Sets

All analyses will be conducted on the Intention-To-Treat (ITT: all enrolled patients undergoing the neurorehabilitation procedure) and Per-Protocol (PP: all patients completing the study without major protocol deviations) populations. All measured variables and derived parameters will be individually listed and, if appropriate, tabulated by descriptive statistics.

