#### 2.4.2. Statistical Analysis

Statistical methods will be in accordance with the CONSORT statement for reporting of randomized trials. Appropriate non-parametric statistics will be used to evaluate the comparability of the intervention and control group at baseline in terms of the clinical characteristics. If, despite the stratified randomization procedure, the groups are not comparable for one or more background variables, those variables will be routinely employed as covariates in the subsequent analyses. The scores for each variable (primary and secondary endpoints) will be calculated according to the published scoring algorithms. Intergroup (effect of the treatment on the measured variable, compared to the control) and intragroup (evolution of the measured variable on the same group) differences in the mean scores over time will be tested using a multilevel analysis. The effect sizes will be calculated using standard statistical procedures. All analyses will be conducted on an ITT basis. PP analyses will also be carried out (as secondary analyses). To test the effectiveness of hippotherapy intervention on functional independence (FIM; primary outcome), non-parametric ANOVA measures for non-linear scores (Friedman’s test for paired data) will be conducted. In addition, to test the effectiveness of the intervention on the secondary outcome variables, including the caregivers’ measurements, non-parametric ANOVA procedures (Friedman’s test for paired data) will also be applied. Post hoc analyses (e.g., additional correlation and covariance statistical procedures) will be conducted according to the obtained results. They will fine-tune the initial data analysis by taking into account potential confounding factors. Given the power of the study (80%), the post hoc results will be statistically robust and therefore reliable. The threshold of statistical significance will be *p* = 0.05. The statistical analyses will be implemented by the CRO using SAS^®^ software (version 9.4, SAS Institute, Cary, NC, USA).

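### Two unranked methods cover the FIM, and the one tied to it by name, Friedman's test, would in its standard three-visit form drop every patient with a missing visit, against the stated ITT basis

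*Protocol article*

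**What the plan says.** All passages are in the protocol article.

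- Section 2.4.2 gives a general method for every primary and secondary endpoint: between-arm and within-arm "differences in the mean scores over time will be tested using a multilevel analysis".
- The same section sets the analysis basis: "All analyses will be conducted on an ITT basis". Per-protocol analyses are secondary.
- It then turns to the FIM, which it labels the primary outcome, and says that "non-parametric ANOVA measures for non-linear scores (Friedman’s test for paired data) will be conducted". The same test is named for the secondary outcomes.
- Section 2.4.1 defines the main set as "ITT: all enrolled patients undergoing the neurorehabilitation procedure", with no condition on later visits. The per-protocol set is those who complete the study without major deviations.
- Section 2.1.2 gives the FIM two time frames, baseline to week 22 and week 22 to week 48, so the FIM is measured at three visits.
- Section 2.1.4 requires 44 evaluable patients and states: "We will recruit 52 patients into the study, to allow for an attrition rate of around 20" percent.

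The article does not say which of the two methods is primary for the FIM, whether Friedman's test spans two or three visits, or when the attrition is expected.

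**The concern.** Friedman's test ranks the visits within each patient. In its standard form it needs a value at every visit, so a patient without a week-48 FIM leaves the test altogether and takes an observed week-22 FIM along. The population left is close to the completers, which is how 2.4.1 describes the per-protocol set and not the ITT set. So this is more than a missing-data rule left to the analysis plan: one of the two named methods, and the one attached to the primary outcome, already decides which patients count, and does so against the declared basis.

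At stake is which patients support the FIM conclusion. In a trial of 52, losing 8 to 10 patients matters for precision. If loss is related to recovery and differs between arms, restricting a comparison to patients seen at every visit can also bias it. Unequal loss is conceivable, because only the hippotherapy arm attends a second site for three cycles, but the documents give no figure for it.

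**Working it through.** **1. What the test does with a missing visit.** A small data set of four patients and three visits, with one week-48 value missing, was put through a standard Friedman routine. The statistic came back undefined. After removal of the incomplete patient it could be computed (statistic 6.0 on three patients).

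**2. How many patients this concerns.** Inputs from 2.1.4: 52 recruited, 44 required, attrition around 20%.

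- Loss implied by the plan's own two counts: 1 − 44/52 = 15.4%, or 8 patients.
- Loss at the stated rate: 52 × 0.20 = 10.4, about 10 patients, leaving 52 × 0.80 = 41.6.
- The two do not agree (44/0.80 = 55, not 52), so 8 to 10 is given as a range.

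**3. How many of these would have a week-22 FIM.** The timing of loss is not stated.

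- All lost before week 22: 0 patients.
- All lost after week 22: about 10 patients.
- Constant rate over 48 weeks (assumption): retained at week 22 is 0.80^(22/48) = 0.903. Lost by then: 9.7% × 52 = 5.1. Lost between weeks 22 and 48: (0.903 − 0.800) × 52 = 5.3, so about 5 patients.

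**4. Precision of a complete-case between-arm comparison.** Inputs from 2.1.4: difference 22, SD 28.43, two-sided 5%, so d = 22/28.43 = 0.774. The plan's own figure does not reproduce from these inputs: 2 × [28.43 × (1.960 + 0.842)/22]² = 26.2, so 27 per arm, or 28 per arm with the t distribution, against the stated 22. That is a separate matter; here the inputs serve only to compare analysis sets. Power by the noncentral t distribution:

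| Patients analysed at week 22 | Per arm | Power |
|---|---|---|
| All 52 | 26 | 78% |
| All with a week-22 value, half of the 20% lost later (52 × 0.90/2 = 23.4) | 23 | 73% |
| Only those with all visits (52 × 0.80/2 = 20.8) | 21 | 69% |

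The avoidable loss is about 4 percentage points of power, under the assumed half-and-half split.

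**5. Bias of a complete-case between-arm comparison.** Simulation: 4,000 runs, 26 per arm, SD 28.43, no true difference. Week-48 loss was 30% in the hippotherapy arm and 10% in the control arm, with the probability of loss weighted by exp(−f·z), where z is the standardised week-22 FIM. The loss rates and f are assumptions.

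| Analysis of week-22 FIM | Mean difference, f = 1 | Mean difference, f = 2 | Rejection at 5% |
|---|---|---|---|
| Patients with all visits only | +5.1 | +7.4 | 10% and 19% |
| All week-22 values | near 0 | near 0 | 5% |

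A repeat with independent code gave +5.3 and +6.9 points, with rejection of 11% and 17%. With loss unrelated to the FIM there was no bias.

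Steps 4 and 5 describe a complete-case test between arms. They are not properties of Friedman's test, which yields no between-arm difference.

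**The case against.** The strongest reply is that 2.4.2 already plans a between-arm analysis that covers the FIM and need not drop anyone, namely the multilevel model. This stands in large part: exclusion follows for Friedman's test only, and a reader who infers that the whole FIM analysis is confined to completers goes beyond the text. What remains is that the section ties the FIM, by name and as primary outcome, to the other method and does not rank the two.

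Second, a three-visit, complete-block form is not certain. The two time frames in 2.1.2 could be tested separately, and the same test is named for outcomes with only a baseline-to-week-22 time frame. Run on those two visits, it would keep every patient with a baseline and week-22 FIM. A stratified rank form of the test can also keep incomplete patients. This stands, and the point is therefore conditional.

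Third, the bias and power figures belong to a test that the plan does not name. This is right. They show why a complete-case replacement would not cure the fault.

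Some stronger readings are tempting but not supported:

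- That patients who leave have no FIM. They have a baseline value and may have a week-22 value.
- That deaths alone would remove a sizeable share. The Introduction's statement, "Mortality is about 15% by 1 month, 25% by 1 year, and 50% by 5 years", concerns stroke in general. Trial patients enter more than 3 and up to 12 months after stroke and are screened for, among other things, fitness for physical activity and travel, so these rates do not carry over.
- That the plan is faulty for giving death no place on the FIM ("A final total score is obtained ranging from 18 (complete dependence/total assistance) to 126 (complete independence"), or for naming no sensitivity analysis. Such rules are commonly left to the full protocol or analysis plan.
- That withdrawn patients are written off. Section 2.2.1 says "In case of a patient’s withdrawal, he/she will continue to benefit the planned care with no impact on its quality", and does not say that assessments stop. The attrition rate is a sizing allowance, not a follow-up rule.

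**Conclusion.** The point holds in a limited form. Section 2.4.2 leaves two methods for the FIM unranked, and the one attached by name to the primary outcome would, in its standard form over three visits, exclude about 8 to 10 of 52 patients. Of these, 0 to about 10 would have a valid week-22 FIM. That cannot be squared with the ITT statement in the same section. The conclusion rests on the standard form, on the test spanning all three visits, and on attrition at the planned level.

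The documents do not show that the planned FIM result is biased. The 5 to 7 points apply to a complete-case between-arm test under an assumed, outcome-related loss of 30% versus 10%. With random loss, the cost of such a test is precision only. The matter is separate from the fact that Friedman's test does not compare arms: a between-arm test restricted to complete cases would cure that defect and keep this one. The change should be made, since it is cheap and removes a contradiction in the primary analysis.

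**What to change.** In 2.4.2, name the between-arm multilevel model already there as the single primary analysis of the FIM. State that the result is the arm-by-visit contrast at week 22, and that the model is fitted to all randomised patients with all their available visits. State also that the FIM conclusion will not rest on a complete-block or complete-case test; if Friedman's test is kept, describe it as a supportive within-arm description.

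The model uses every observed week-22 FIM. For patients lost before week 22 it relies on their loss being explained by the data observed, which is a weaker demand than that of a complete-case analysis.

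The cost is analysis wording only, with no new visits or measurements. The downside is a result that may be slightly less favourable than one based on completers.

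### Section 2.4.2 infers from the study's 80% power that post hoc results will be reliable; that power was derived for one FIM comparison and does not support the inference

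*Protocol article*

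**What the plan says.** Section 2.4.2 (Statistical Analysis) first sets out the tests for FIM and for the secondary outcomes, and then turns to post hoc analyses. These "will be conducted according to the obtained results", and the examples given are "additional correlation and covariance statistical procedures". Their stated purpose is to refine the initial analysis by allowing for possible confounders. The section then says: "Given the power of the study (80%), the post hoc results will be statistically robust and therefore reliable". The next sentence sets one threshold for significance, p = 0.05 ("The threshold of statistical significance will be"). Nothing in the section calls the post hoc analyses exploratory.

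The 80% comes from section 2.1.4 (Sample Size and Recruitment). It rests on a "minimum reasonably significant difference in the primary outcome (Functional Independence Measure) of 22 points", "with a standard deviation of σ = 28.43". The calculation reads "To detect that difference with a power of 80% using a two-sample" t-test, two-sided at 5%, with 44 patients (22 per arm).

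**The concern.** Power is the probability that a specified test, at a specified level, detects an effect of a specified size. It belongs to that test and that effect. The protocol treats it as a property of the whole study that makes any later analysis trustworthy. Two things are wrong with this.

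- **It does not transfer.** A correlation between two measures, or a model with covariates chosen later, has its own effect size, variance and power. The FIM calculation says nothing about them.
- **It addresses the wrong error.** Power concerns missed effects. The main hazard of analyses chosen after seeing the results is the false positive, and power does not limit that.

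What is at stake is interpretation. A reader of the results who follows the protocol's own words would give result-driven findings a reliability that the design does not provide.

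**Working it through.** **Step 1. What the 80% refers to.** Inputs from section 2.1.4: difference 22, SD 28.43, 22 per arm, two-sided 5%. The standardised difference is 22 / 28.43 = 0.774.

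Power by the normal approximation is Φ(0.774 × √(22/2) − 1.96) = Φ(2.567 − 1.960) = Φ(0.607) = 72.8%. The noncentral t calculation gives 70.8%. The stated 80% is therefore not reproduced from its own inputs. That is a separate sample-size matter, and the present point would stand if the 80% were exact. What matters here is that every input describes a single between-arm comparison of FIM. No correlation, covariance model or other outcome enters the calculation.

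**Step 2. False positives in analyses chosen later.** The protocol does not say how many post hoc tests there will be, so the number k is my assumption. For k independent tests of true null hypotheses, each at 0.05, the chance of at least one significant result is 1 − 0.95^k.

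| k (assumed) | 1 − 0.95^k |
|---|---|
| 5 | 22.6% |
| 10 | 40.1% |
| 20 | 64.2% |

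The study's power does not appear in this formula, so raising it from 71% to 80%, or to 99%, would leave the table unchanged. Independence is also an assumption. Positively correlated tests, such as several adjusted versions of the same FIM comparison, give lower figures.

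**Step 3. Power of a post hoc correlation.** Correlation is one of the two types of procedure that the section gives as examples. By the Fisher z approximation with N = 44, power is about Φ(atanh(r) × √(44 − 3) − 1.96), where √41 = 6.403. The values of r are assumptions.

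| r (assumed) | atanh(r) × 6.403 | minus 1.96 | Power |
|---|---|---|---|
| 0.2 | 1.298 | −0.662 | 25% |
| 0.3 | 1.982 | 0.022 | 51% |
| 0.4 | 2.713 | 0.753 | 77% |

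A correlation of about 0.41 would be needed for 80% power: tanh((1.960 + 0.842) / 6.403) = 0.41. For smaller correlations, power falls short of the figure the sentence relies on.

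**The case against.** The best case for the text has four parts.

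- **The label.** The analyses are called post hoc and are listed after, and apart from, the primary and secondary tests. A trained reader already knows that such analyses are not pre-specified. This is true, but the sentence then tells that reader to treat them as reliable, which undoes the label.
- **The purpose.** They are described mainly as adjustment for confounders, not as a search for new effects. This stands in part. Adjusted versions of one comparison are strongly correlated, so the independent-test figures overstate the error for them. But choosing covariates in the light of the results is itself data-driven, and the named procedures are examples, not a closed list.
- **The unseen analysis plan.** Multiplicity control and a test order may be set there. This stands, and nothing here rests on their absence. The fault is a false statement in the protocol, and an analysis plan that followed it would inherit it.
- **The limited reach.** The sentence changes no endpoint, sample size, test or decision rule. This also stands, and it limits the seriousness of the point.

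A reader might go further and infer that the sentence licenses confirmatory claims, or that the trial's conclusions and the guideline ambitions in section 4 would rest on post hoc findings. The text does not support that. It never uses the word confirmatory, it tests effectiveness on FIM, and section 4 does not tie those ambitions to post hoc results. Nor does section 2.4.2 propose subgroup or interaction analyses, so their power is not at issue. The number of planned secondary tests is a different matter, because those endpoints are pre-specified.

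**Conclusion.** The point holds in a narrow form. The sentence is wrong as written: 80% power for one FIM contrast does not make result-driven analyses robust or reliable, and nothing else in the document corrects it. This does not depend on any figure above.

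The sizes are illustrations. The 23% to 64% chance of at least one false positive assumes 5 to 20 independent null tests at 0.05, and it is lower under correlation. The 25% to 77% power assumes 44 patients and true correlations of 0.2 to 0.4. The protocol fixes none of the numbers of tests or the correlations, so these are not properties of this trial. The planned FIM comparison is unaffected. The error concerns only how later findings would be read, and it should be corrected before the analysis.

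**What to change.** Delete the sentence in section 2.4.2 that links power to the post hoc results. Replace it with a statement that:

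- post hoc analyses are exploratory and serve to generate hypotheses;
- they are reported as estimates with 95% confidence intervals;
- they do not support the conclusion on effectiveness, which rests on the pre-specified FIM comparison.

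The cost is one replaced sentence. Design, sample size, data collection and planned tests stay as they are. The only downside is that exploratory results are described less favourably than now.

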## 3. Discussion

Scientific evidence has gradually emerged in recent years, showing the benefits of hippotherapy in various severe brain disabling conditions, including stroke [11,12,13,14,15,16,17,18,19,20,21,23,24,25,26,27,59]. An increasing number of studies on the hippotherapy treatment of neurological sequelae of acquired brain injuries are published, but their methodological quality is rather low. In general, they report the beneficial effects on posture, walking, spasticity, and gross and fine motor skills, but these positive effects are challenged by the difficulties in establishing sound methodological frameworks. The present protocol is the result of a decade of clinical hands-on practice and research. The rationale of this cutting-edge method considers motion as a key driver of short- and long-term neurorehabilitation strategies. It could be hypothesized that movement could promote a reshaping of brain functions, thanks to the up/down regulation of the synthesis and release of neuroactive substances (e.g., BDNF, VIP, GABA, endomorphin 1 and 2, α-MSH, serotonin, and dopamine) synthesized in the enteric nervous system, which would physiologically impact the entire cerebral metabolism fostering neuroplasticity [27,60,61].

Each horse conveys a specific movement at a walk [22,62,63]. The therapeutic strategy here consists of thoroughly evaluating the patient’s condition and deciding what movement is most suitable to release the potential psychic/cognitive (silent patient’s blockages) and functional (trunk hypertonia, inefficient postural balance, postural tilt, pelvic locking, shoulder asymmetry, attentional lability, executive dysfunctions, and deficit in spatial awareness) barriers. By identifying the very first step of the process, the therapist would be able to trigger the sequence and progressively unlock the neuro-functional capacities (e.g., trunk motion and modulation of postural reflexes through the setup of the alternating contraction of postural muscles, depending on micro-movements elicited by the horse at a walk). Simultaneously, the reinforcement of the cognitive sphere (e.g., executive functions, attention, and working memory) could be efficiently targeted and tailor-made. Some of the clinical hypotheses on which this project is built have been strengthened and confirmed through several quantitative research protocols on postural kinetics and electromyography [11,12].

Hippotherapy gradually emerges as a cutting-edge solution for human impairment, activity limitation, and participation restriction. The main objective of the clinical trial, which relies on the protocol presented in the present study, will be to validate hippotherapy as a novel approach to stroke neurorehabilitation consisting of a personalized all-inclusive rhythm-adapted patient’s empowerment, which constantly re-evaluates and adjusts itself in real time, according to the patient’s neurological possibilities, his/her interaction with the family caregiver(s) and his/her lifetime goals.

